### 11.3 DEFINITIONS REQUIRED FOR FOLLOW-UP

**Complete response** is defined as undetectable disease at the site of the primary tumour following pre-operative chemotherapy and/or radiotherapy. A pre-fix to denote the mode of assessment must also be included - clinical (c), MRI (mr) and pathology (p).

**Disease recurrence** is defined as either evidence of loco-regional recurrence or established metastatic disease. The time to the event is measured from the start of chemoradiotherapy to the date of the diagnostic investigation or MDT.

**Regrowth** is defined as the first recorded evidence of disease at the site of the primary tumour, in a patient with previous investigations suggesting an apparent complete response or undetectable disease (mrTRG1&2). The terms 'early regrowth' and 'late regrowth' will not be used in the trial.

**Unsalvageable regrowth** is defined as a tumour with radiological evidence of a good response that is initially managed by deferral of surgery but progresses. The extent of progression means that pCRM involvement becomes inevitable and so surgery is not performed, or pCRM involvement occurs when surgery is attempted.

**Loco-regional recurrence** (one of):

- Clinical recurrence with biopsy proof of recurrence
- CEA elevation and enlarging or new mass (includes pelvic, nodal and peritoneal disease). Biopsy confirmation is contraindicated or not feasible
- CEA non-secretors: enlarging or new mass (includes pelvic, nodal and peritoneal disease). Biopsy confirmation is contraindicated or not feasible (with or without PET/CT confirmation)

**Distant Metastases** (one of):

- This is defined as any confirmed evidence of disease above the L5/S1 junction
- Clinical recurrence with biopsy proof of recurrence
- CEA elevation and evidence of distant metastases. Biopsy confirmation is contraindicated or not feasible

- CEA non-secretors: evidence of distant metastases. Biopsy confirmation is contraindicated or not feasible (with or without PET/CT confirmation). Initial report to Trials Unit should define this as SUSPECTED. A further report 6 months later should define this as CONFIRMED if supported by MDT review.

***Inoperable Disease*** (one of):

- MDT decision that the local extent of disease on the post CRT pelvic MRI is not resectable
- At laparotomy the local extent of disease is not resectable
- Incomplete resection of tumour at laparotomy after pre-operative CRT with biopsy proof of residual disease. (Lack of biopsy proof in this situation would constitute “suspected” persisting disease)

***Suspected Regrowth:*** When clinical assessment, CEA values, Radiological investigations and Endoscopic assessment lead to an equivocal diagnosis of regrowth, please indicate this in the allocated box on the **SURVEILLANCE Form indicating an equivocal diagnosis** and submit this form to the trial office.

## **11.4 COMPLIANCE WITH THE PROTOCOL**

The investigators and sponsor will agree to implement the study protocol as written. The study will be performed in accordance with the clinical trials regulations, the Declaration of Helsinki and the principles of GCP.

## **11.5 DEFINITION OF END OF TRIAL**

The end of the trial is defined as the last patient’s last visit.

# **12 DATA MANAGEMENT**

## **12.1 COMPLETING CASE REPORT FORMS**

Trial data will be recorded on version controlled Case Report Forms (CRF pack) by staff included on the site Delegation Log who are authorised to make entries and/or corrections on CRFs. Data entered onto CRFs must reflect source data at site. Source documents are original documents, data, and records from which the patient’s CRF data are obtained. These include but are not limited to hospital records, clinical and hospital charts, laboratory and pharmacy records, images and correspondence. Case report entries may be considered source data if the CRF is the site of the original recording i.e. there is no other written or electronic record of data. In this situation the CRFs may be used as source documents for the purpose of this trial. The PI is responsible for the accuracy of all data reported in the CRF.

The list of CRFs required during the trial and the completion timelines are included at the front of the CRF pack and included in the Assessment schedules above. Once completed these should be sent to **the TRIGGER Trial Office** at the Royal Marsden and the original retained at site.

## **12.2 CORRECTIONS TO CASE REPORT FORMS**

Any corrections made to a CRF must be made by drawing a single line through the incorrect item ensuring that the previous entry is not obscured. Each correction must be dated and initialed. The amended CRF must be sent to the TRIGGER Trial Office and a copy retained at site.

## **12.3 MISSING DATA**

To avoid the need for unnecessary data queries CRFs must be checked at site to ensure there are no blank data fields before sending them to the TRIGGER Trial Office. Please use the following acronyms as appropriate:

- **ND** - for not done - when data are unavailable because a measure has not been taken or a test not performed.
- **NA** – for not applicable – if a measure or test was not required at a particular time the form relates to.
- **NK** – for not known – when data are unknown (only use if every effort has been made to obtain data).

## **12.4 DATA QUERIES**

Data arriving at the TRIGGER Trial Office will be checked for completeness, accuracy and consistency. Queries on incomplete, inaccurate or inconsistent data will be sent to the appropriate contact at the study site. When responding to a query, site staff should attach an amended copy of the CRF as appropriate and a copy retained at site. All amendments must be initialled and dated.

## **12.5 SUBMISSION TIMELINES**

All CRFs must be completed at site and returned to the TRIGGER Trial Office as soon as possible after the patient visit and within one month of the patient being seen.

## **12.6 DATA COLLECTION AND RETENTION**

The investigator and trial staff are responsible for maintaining a comprehensive, centralised and secure filing system of all trial-related documentation, suitable for trial-related monitoring, audits or inspection at any time by representatives from the sponsor and/or regulatory authorities. Trial documentation includes original source documents, patient files containing completed CRFs and informed consent forms, patient identification list and site investigator site file.

No trial documentation should be destroyed without prior written agreement between the sponsor and the investigator. Should the investigator wish to assign the study records to another party or move them to another location, he/she must notify the sponsor in writing of the new responsible person and/or location.

The Sponsor should ensure that all trial related documentation be retained for the maximum period of time as specified in the UK Clinical Trial Regulations.

## **12.7 TRIAL DATABASE**

Patients' data will be documented on a trial specific CRF. Only the Investigator, and those personnel who have completed the Study Team Delegation Log as authorised by the PI, should enter or change data on the CRF. The data will be entered in a clinical trials database (Macro V4). Data entry will be carried out by appropriately trained personnel. Data clarification queries will be raised centrally by the trial manager and sent to each participating centre for resolution. Access to the study database is restricted to the appropriate data managers and statisticians.

## **13. TRIAL MONITORING AND OVERSIGHT**

Participating sites and Principal Investigators must agree to allow trial-related on-site monitoring, including Sponsor audits and regulatory inspections by providing direct access to source data/documents as required. Patients are informed of this in the patient information sheet and are asked to consent to their medical notes being reviewed by appropriate member(s) from the TRIGGER Trial Office, or from regulatory authorities or from the NHS Trust on the consent form.

### **13.1 SELF-ASSESSMENT MONITORING**

Participating sites will be requested to complete a Trial Self-Assessment Monitoring form periodically, at a frequency detailed in the Trial Monitoring Plan. This report may include, but is not limited to:

- Investigator Site File document review
- Pharmacy Site File document review
- Recruitment status
- Review of Informed Consent Forms
- Pharmacovigilance review

Responses will be reviewed at the TRIGGER Trial Office to identify any areas of non-compliance/fraud and to indicate training needs. Findings may trigger an on-site monitoring visit.

## 13.2 CENTRAL MONITORING

Site requirements for the purpose of central monitoring are summarised in the table below.

| Site responsibility                                                       | Frequency                                                                                                         | Central Monitoring                                                                                                                                                                   |
|---------------------------------------------------------------------------|-------------------------------------------------------------------------------------------------------------------|--------------------------------------------------------------------------------------------------------------------------------------------------------------------------------------|
| Send copy of delegation log                                               | Every 3 months and every time the log is updated (addition or removal of trial staff, change in responsibilities) | To confirm adequate number of staff and delegated responsibilities appropriate. Confirm only staff with delegated responsibility are taking informed consent.                        |
| Send copy of patient eligibility checklist (included in REGISTRATION CRF) | At the time of patient registration                                                                               | To confirm eligibility                                                                                                                                                               |
| Send copy of patient consent form at registration and randomisation       | At registration and randomisation                                                                                 | Verify existence of patient                                                                                                                                                          |
| Send copies of screening, registration and randomisation logs.            | Every 3 months.                                                                                                   | To check for consistency and completeness and evaluate screen failure rate and reasons for non-inclusion at each stage.                                                              |
| Send Case Report Forms*                                                   | Each time a form is completed.                                                                                    | To allow checks for missing and unusual values and consistency over time, and generate data queries as appropriate. To ensure data is entered onto trial database in timely fashion. |

\*Data stored at the TRIGGER Trial Office will be checked for missing or unusual values (range checks) and checked for consistency over time. If any problems are identified data queries will be issued to the site. Sites are required to resolve any queries and update the relevant CRF as required. All changes must be initialled and dated. The amended version must be sent to the TRIGGER Trial Office and a copy retained at site.

## 13.3 NON-COMPLIANCE/'FOR CAUSE' ON-SITE MONITORING

On-site monitoring visits may be scheduled where there is evidence or suspicion of non-compliance at a site with important aspect(s) of the trial protocol/GCP requirements. Sites will be sent a letter in advance outlining the reason(s) for the visit, a list of the documents that are to be reviewed, interviews that will be conducted, planned inspections of the facilities, who will be performing the visit and when the visit will likely occur.

Following a monitoring visit, the Trial Manager will provide a report to the site, which will summarise the documents reviewed and a statement of findings, deviations, deficiencies, conclusions, actions taken and actions required. The Principal Investigator at each site will be responsible for ensuring that monitoring findings are addressed (this may be delegated to an appropriate member of staff).

The TRIGGER Trial Working Group will assess whether it is appropriate for the site to continue participation in the trial and whether the incident(s) constitute a serious breach. See Appendix 1 (Incident Reporting and Serious Breaches) for details.

## **13.4 OVERSIGHT COMMITTEES**

### **13.4.1 TRIAL MANAGEMENT GROUP (TMG)**

The TMG will include the Chief Investigator, the Royal Marsden Hospital PI and CTIMP lead, the Principal Clinical Coordinator/Investigator, clinicians and experts from relevant specialities and trial staff from the TRIGGER Trial office (list of members included on page iv). The TMG will be responsible for overseeing the trial. The group will meet regularly (at least 4 times per year – with greater frequency at the start of the study) and will send updates to Principal Investigators (via newsletters and/or at Investigator Meetings).

The TMG will agree protocol amendments on behalf of the PIs prior to submission to the REC and MHRA. All PIs will be kept informed of substantial amendments through their nominated responsible individuals.

### **13.4.2 INDEPENDENT DATA MONITORING AND ETHICS COMMITTEE (DMEC)**

The role of the DMEC is to provide independent advice on data and safety aspects of the trial. During the study, interim analyses of safety and outcome data will be supplied, in strict confidence, to an independent Data Monitoring and Ethics Committee (DMEC) along with any other analyses that the committee may request.

The DMEC will meet annually, or more frequently if considered appropriate, and will advise the chair of the TMG if, in their view, the randomised comparison in TRIGGER has provided both (a) “proof beyond reasonable doubt” that for all, or for some types of patient, treatment mrTRG directed management is clearly indicated or clearly contraindicated in terms of a net difference in the main outcome measures, and (b) evidence that might reasonably be expected to influence the patient management by many clinicians.

The TMG can then decide whether to modify the study protocol. Unless this happens, however, the TMG, the collaborators and all of the central administrative staff (except the statisticians who supply the confidential analyses) will not be informed of the DMEC analysis.

If the clinical coordinators are unable to resolve any concern satisfactorily, collaborators, and all others associated with the study, may write via the TRIGGER trial office to the chair of the DMEC, drawing attention to concerns about the possibility of particular side-effects, or of particular categories of patient requiring special study, or about any other matters thought relevant.

### **13.4.3 ROLE OF THE ROYAL MARSDEN NHS FOUNDATION TRUST**

The TRIGGER Trial Office at the Royal Marsden will be responsible for the day to day coordination and management of the trial and will act as custodian of the data generated in the trial. The Royal Marsden NHS FOUNDATION TRUST, as sponsor, is responsible for all duties relating to pharmacovigilance which are conducted in accordance with Appendix 1 (Safety Monitoring Procedures).

## **14. STATISTICAL ANALYSIS AND SAMPLE SIZE**

### **14.1 SAMPLE SIZE**

#### **14.1.1 PHASE III STUDY SAMPLE SIZE**

A detailed sample size calculation will be included in the phase III protocol. However the expected sample size is estimated here in order to calculate the required recruitment rate, which is the primary endpoint of this protocol.

It is anticipated that the phase III trial will be designed to detect an improvement in 3 year DFS in the intention to treat population from 74% to 82% (i.e. a hazard ratio of 0.66) with 80% power and a 5% 2-sided level of statistical significance. This would require 633 patients (422 in the intervention arm and 211 in the control arm based on 2:1 allocation ratio) to be recruited over 3 years with at least 3 years follow up to observe the 184 events required. The final sample size for the phase III trial may differ depending on a number of factors including results of the feasibility trial.

#### **14.1.2 FEASIBILITY STUDY SAMPLE SIZE**

In this feasibility study a type II error would result in the cancellation of the planned phase III study when the recruitment rate was in fact sufficient to support such a study. We wish to minimise the probability of this occurring and so have set the chance of a type II error (B) at 5% and the resulting power (1-B) at 95%. A type I error would result in the planned phase III study going ahead when the true recruitment rate is poor. We would accept a 10% chance of this occurring and so have set the significance threshold (alpha) at 0.1.

The sample size for the primary endpoint of the feasibility study can be worked out as follows:

Recruitment of at least 633 patients to the phase III trial is planned to take place over a total of 3 years, and should take at most no more than 5 years. Hence the recruitment rate is expected to be 11 patients per month and will need to be no less than 5-6 patients per month (5/month results in total time of 6.5 years,

6/month results in 5.5 years total). In a similar multicentre trial sponsored by RM (6 vs. 12), recruitment rates over time were as follows:

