## 14. 2 ANALYSIS METHODS

### 14.2.1 PRIMARY ENDPOINT

The primary endpoint of this study is the total numbers of patients randomised per month, during the last 4 months of recruitment. A chi-squared goodness of fit test with one-sided alpha of 0.1 will be used to test the null hypothesis that the expected number of patient recruitment per month is equal to 6. Rejection of the null hypothesis would suggest that recruitment levels are adequate to support the proposed phase III study with sample size and length of recruitment as described in this protocol. However if the null hypothesis is not rejected then exact recruitment rates by time for each centre will be stated, and any known reasons for low recruitment investigated. After taking these results into consideration it may still be deemed possible to proceed with a phase III study if the design is amended accordingly. The primary endpoint for the feasibility study will be stated in full in the phase III protocol before seeking final approval.

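### The recruitment rates tested (null 6, alternative 11 per month) do not follow from 633 phase III patients in 3 to 5 years, so rejecting 6 per month is not by itself evidence of timely accrual

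*Protocol*

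**What the plan says.** Section 14.1.1 sizes the anticipated phase III trial: "This would require 633 patients (422 in the intervention arm and 211 in the control arm based on 2:1 allocation ratio"), to detect a change in 3-year disease-free survival "from 74% to 82% (i.e. a hazard ratio of 0.66) with 80% power and a 5% 2-sided level of statistical significance", the patients "to be recruited over 3 years with at least 3 years follow up to observe the 184 events required".

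Section 14.1.2 carries that number forward: "Recruitment of at least 633 patients to the phase III trial is planned to take place over a total of 3 years", with an upper limit of 5 years. From this it concludes: "Hence the recruitment rate is expected to be 11 patients per month and will need to be no less than 5-6 patients per month". In brackets it gives 6.5 years at 5 per month and says "6/month results in 5.5 years total". It then uses a mean of 11 as the alternative and 6 as the null in the simulation that fixes the 4-month window.

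Section 14.2.1 tests the null of 6 at one-sided 0.1 and interprets the result: "Rejection of the null hypothesis would suggest that recruitment levels are adequate to support the proposed phase III study", for the sample size and recruitment length that the protocol describes. Section 3.1 makes 6 per month in the last four months one of two conditions for continuing (the other is funding) and says that feasibility patients will enter the phase III analysis. The trial summary plans 90 feasibility patients.

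**The concern.** The primary endpoint exists to decide whether phase III can recruit in time. Section 14.1.2 presents its two rates as consequences of 633 patients and the 3- and 5-year periods, but they do not follow. Even taken at face value, 5.5 and 6.5 years both exceed the 5-year limit set just before them.

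At stake is the meaning of a pass. Section 14.1.2 accepts a 10% chance of going ahead when true recruitment is poor. If the null lies well below the slowest rate that meets the protocol's own ceiling, that 10% does not cover rates between the null and that slowest rate. The trial can then report adequate recruitment on a rate that its own figures call too slow.

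**Working it through.** **Inputs.** N = 633; planned 36 months, maximum 60 months; rates 5, 6 and 11 per month (14.1.1, 14.1.2). Sensitivity: all 90 feasibility patients credited, so N = 633 − 90 = 543 (trial summary, 3.1).

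**Is 633 the faulty number?** No. With exponential disease-free survival, uniform 3-year accrual (a) and 3-year minimum follow-up (f), expected events per arm are n·{1 − [exp(−λf) − exp(−λ(f+a))]/(λa)}, with λ = −ln(0.74)/3 for control and −ln(0.82)/3 for intervention. This gives 76.2 of 211 and 108.1 of 422, together 184.3, against the stated 184.

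**Required rate = N / months**

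| | 3 years | 5 years |
|---|---|---|
| N = 633 | 633/36 = 17.6 per month | 633/60 = 10.55 per month |
| N = 543 | 543/36 = 15.1 per month | 543/60 = 9.05 per month |

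**Accrual time = N / rate / 12**

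| Rate per month | Stated | N = 633 | N = 543 |
|---|---|---|---|
| 5 | 6.5 years | 126.6 months = 10.6 years | 9.05 years |
| 6 | 5.5 years | 105.5 months = 8.8 years | 7.5 years |
| 11 | 3 years (implied) | 57.5 months = 4.8 years | 4.1 years |

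The stated figures are not reproduced with either N. Even the intervention arm alone (422) takes 5.9 years at 6 per month. The stated pairs do agree with one another at about 390 to 396 patients: 11 × 36 = 396, 6 × 66 = 396, 5 × 78 = 390.

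**Null against the 5-year rate.** 6/10.55 = 57%; with credit 6/9.05 = 66%.

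**What a pass shows, if the test is a one-sided exact Poisson test on the 4-month total.** Under the null the mean is 24. P(total ≥ 30) = 0.132 and P(total ≥ 31) = 0.096, so rejection starts at 31 patients, or 7.75 per month. At that rate 633 patients take 6.8 years and 543 take 5.8. Totals of 31 to 42 (10.5 per month) reject the null but miss 5 years for 633; with credit the range is 31 to 36 (9.0 per month). At a true 9 per month (5.9 years for 633; 543/9/12 = 5.03 years for 543), P(total ≥ 31 | mean 36) = 82%.

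**If the test is the goodness-of-fit test simulated in 14.1.2.** The statistic is the sum over four months of (x − 6)²/6. The stated 95 to 96% power is reproduced with 3 degrees of freedom (95.9%; 93.1% with 4). There is no single cut on the total: counts 9, 9, 9, 9 (total 36) give 6.0 and do not reject (critical values 6.25 and 7.78), whereas 0, 6, 6, 12 (total 24) give 12.0 and do. By simulation, a true 9 per month passes about 64% of the time with 4 degrees of freedom and about 74% with 3.

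**Rates recomputed from 633, exact one-sided test on the same 4-month total**

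| | H0 / H1 per month | Cut | Type I error | Power | P(go) at a true 11 |
|---|---|---|---|---|---|
| N = 633 | 10.55 / 17.6 | 52 | 8.0% | 99.0% | 13% |
| N = 543 | 9.05 / 15.1 | 45 | 8.7% | 98.3% | 46% |

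**The case against.** The best defence is that the decision has buffers. Section 14.1.1 says the final phase III size may change, section 3.1 also requires funding and a substantial amendment, and section 14.2.1 says only that rejection would suggest adequacy. All of that is true, so a go is not automatic. It does not cure the error: the rates are derived explicitly from 633, and 14.2.1 ties adequacy to the size and length described. The redesign route in 14.2.1 applies when the null is not rejected, whereas the problem here is a pass at too slow a rate.

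Three stronger readings are tempting, and the documents do not support them.

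- A reader might infer that passing can never show feasibility. It can: an observed 10.55 per month or more (9.05 with credit) meets the 5-year maximum, and 11 per month fills the trial in 4.8 years.
- A reader might take 31 patients as the trial's pass mark. That holds only for a one-sided test on the 4-month total. The wording on the average rate (14.1.2) and the one-sided alpha (14.2.1) can support such a test, but the simulated test works on four separate counts.
- A reader might conclude that the rates were left over from a smaller planned trial. The 390 to 396 pattern suggests this, but no passage says so.

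**Conclusion.** The figures are wrong as written and need correction, because they form the null and alternative of the only primary endpoint and the gate in section 3.1. Accrual at 6 per month is understated by 3.3 years (8.8 against 5.5) and at 5 per month by 4.1 years (10.6 against 6.5). The rate labelled as expected is close to the slowest that meets the 5-year limit, and the rate labelled as the minimum is well below it.

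The conclusion is limited to this: rejecting 6 per month is not sufficient on its own to show that the described phase III can recruit in time. The rates and durations are plain division and rest on no assumption beyond a constant monthly rate. The pass probabilities also assume independent Poisson monthly counts and depend on which test is used. Crediting 90 patients softens the figures but rescues none of the stated durations.

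**What to change.** Correct the durations and required rates in 14.1.2, stating whether feasibility patients are credited. Then make 14.1.2, 14.2.1 and 3.1 agree in one of two ways; the choice is the sponsor's.

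**(a) Keep 6 and 11 per month.** State 8.8 years at 6, 10.6 at 5 and 4.8 at 11 per month. Withdraw the 5-year maximum and the statement that rejection shows adequacy for the size and length described. Alternatively, keep the maximum and add that adequacy within 5 years also requires an observed rate of at least 10.55 per month (9.05 with credit). The cost is wording, and a plainer admission of what a pass means.

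**(b) Reset the null and alternative to the 5-year and 3-year rates:** 10.55 and 17.6, or 9.05 and 15.1 with credit. The 4-month window still suffices, so no patients or months are added. The bar becomes much stricter: at a true 11 per month, which meets the 5-year limit, the chance of a go is 13% (46% with credit). Section 14.1.2 gives priority to avoiding wrongful cancellation, so this is a real cost. Either null also exceeds every monthly rate in the protocol's table from the comparator trial, where the maximum is 7.7.

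Under either option, state in 14.2.1 whether the test uses the 4-month total or the four monthly counts, since the pass mark depends on it.
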